# *3.9.1 Surveillance for adverse events*

An adverse event is defined as any unfavourable and unintended sign, symptom, syndrome, or illness that develops or worsens during the period of observation in the clinical study. Clinically relevant abnormal results of diagnostic procedures including abnormal laboratory findings (e.g., requiring unscheduled diagnostic procedures or treatment measures, or resulting in withdrawal from the study) which are considered by the Principal Investigator to be detrimental should be recorded as adverse events whether or not they have a causal relationship with the study drug. Where the laboratory result is a sign of another clinical condition, the clinical condition itself should be the reported adverse event. An event unequivocally caused by a significant deterioration of the underlying condition related to malaria is regarded as an adverse event.

To determine the prevalence of minor side effects following drug administration such as headache, fever, weakness, abdominal pain, anorexia, nausea, vomiting, diarrhoea, rash, itching or sleep disorder participants in each treatment group will be visited at home three and seven days after each round of drug administration and a side effects questionnaire completed. Field workers who complete these questionnaires will be unaware of the treatment group to which the child belongs. To help establish whether these adverse events are drug related, the same questionnaire will be administered once after each treatment round, to 286 children who are not part of the trial, recruited from nearby villages and matched for age to children in the trial.

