**Summary**

Intermittent preventive treatment (IPT) offers a potential way of preventing malaria infection without compromising the development of malaria immunity or encouraging drug resistance. The effect of IPT in children in the prevention of malaria has been evaluated in a number of trials in areas of seasonal malaria transmission. Results from these trials have shown that IPTc provided between 40% - 86% protection against clinical malaria. In 2006, a trial that compared two methods of IPTc delivery was carried out in Upper River Division, The Gambia. Preliminary results of the trial have shown that the treatment was very effective as only 4% (45/1133) of the children seen at the end of year cross-sectional survey were parasitaemic. Tolerability was assessed in a subset of 1100 children and the results showed that about 13.5% of children developed mild to moderate vomiting. Malaise was present in about 10% of the study subjects. Severe adverse events were rare. Thus it is important to investigate if other drug regimens might be equally effective in preventing malaria but less likely to cause adverse events. During the 2007 malaria transmission season, 1009 children aged 1-5 years will be individually randomized to receive amodiaquine plus SP, piperaquine plus SP or Artekin TM (dihdroartemisinin plus piperaquine) at monthly intervals on three occasions during the months of September, October, and November. To determine the prevalence of side effects following drug administration participants in each treatment group will be visited at home three and seven days after each round of drug administration and a side effects questionnaire completed. To help establish whether these adverse events are drug related, the same questionnaire will be administered after each treatment round, to 286 age-matched children who are not part of the trial. The primary ends points will be the incidence of adverse events.

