# *3.11 End of malaria transmission season cross-sectional survey*

Children enrolled in the study will be seen at the OPD clinic at the end of malaria transmission season for examination by a study physician and a finger-prick blood sample will be obtained for preparation of a thick blood smear and determination of haemoglobin concentration. A standardized questionnaire will be administered to the parents/guardians of the study subject, to collect information regarding illness that had occurred since the last visit, symptoms experienced, use of healthcare facilities and use of medicines. Information on the use of bed nets will be collected again at this visit.

*3.12 Study end-points:*

*3.12.1 Primary end points*

*Safety endpoint*

- Incidence of any adverse events during the observation period.

*Secondary end points*

- Mean Hb (g/dl) at the end of malaria transmission.
- Prevalence of malaria parasitaemia at the end of the malaria transmission season.
- Number of OPD attendances with malaria that meet the case definitions as indicated below during the surveillance period.

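### Untreated comparison children get one side-effects interview per round, on no fixed day, against two for trial children, so the drug-relatedness comparison can show a difference that comes only from interview count

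*Protocol*

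**What the plan says.** Protocol section 3.9.1 sets two interview schedules. For the randomised children, "participants in each treatment group will be visited at home three and seven days after each round of drug administration", and a side-effects questionnaire is completed at each visit. For the untreated group, "the same questionnaire will be administered once after each treatment round, to 286 children who are not part of the trial". These children are "recruited from nearby villages and matched for age to children in the trial".

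The aim of the second group is stated in the same section: "To help establish whether these adverse events are drug related". The Summary repeats the plan without the word for a single interview: "To help establish whether these adverse events are drug related, the same questionnaire will be administered after each treatment round". That is less specific than 3.9.1 but does not conflict with it.

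Treatment is given "at monthly intervals on three occasions during the months of September, October, and November", so a trial child has 2 × 3 = 6 scheduled questionnaires and a comparison child 1 × 3 = 3. The primary endpoint in section 3.12.1 is "Incidence of any adverse events during the observation period".

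The protocol does not fix the post-round day of the comparison interview or the period each questionnaire asks about. It also does not say which trial visit the comparison answers are to be set against.

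**The concern.** When the outcome is whether a child had any event, a second interview can only add children to the count. If the trial arms are summarised over two interviews and the comparison group over one, the treated side is counted more generously whatever the drugs do.

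This matters because no randomised arm is untreated. Section 1.2.3 notes that the 2006 study's vomiting figure of about 13.5% had no control group, and that perceived adverse events reduced compliance. The comparison children are there to fill that gap. A contrast partly produced by interview count could lead readers to attribute ordinary rainy-season symptoms to the regimens.

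**Working it through.** **The plan's own figure.** Section 3.14 has 286 per arm for 20% v 10%, 90% power, significance level 0.05. The two-sided two-proportion formula gives 266 without and 286 with continuity correction, so 286 is reproduced. Allowing for drop-out, 286 × 3 / 0.85 = 1009.4, stated as 1009. The comparison group is also 286.

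**Inputs from the protocol.** Two interviews per round v one (3.9.1); three rounds (Summary); an any-event endpoint (3.12.1); 286 comparison children (3.9.1) and 286 per arm (3.14).

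**Assumed, because the protocol gives no value.** The probability q that an interview is positive without any drug effect, the same in both groups; the correlation ρ between a child's two interviews in a round; independence between rounds; no overlap in what the interviews ask about beyond what ρ represents.

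**Formulas.**
- One interview: q. At least one positive of two: P = 1 − [(1−q)² + ρq(1−q)].
- Over three rounds: 1 − (1−q)³ v 1 − (1−P)³.
- False significance: rejection probability of a two-sided 0.05 two-proportion z-test, 286 v 286, Φ[(d − 1.96·se₀)/se₁] plus the negligible opposite tail, with d the difference, se₀ the pooled and se₁ the unpooled standard error.

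**One case in full (q = 10%, ρ = 0).** P = 1 − 0.81 = 19.0% against 10.0%. se₀ = √(0.145 × 0.855 × 2/286) = 0.0294; se₁ = √[(0.19 × 0.81 + 0.10 × 0.90)/286] = 0.0292. (0.09 − 0.0577)/0.0292 = 1.106, so the probability is 0.866. With ρ = 0.5, P = 1 − (0.81 + 0.045) = 14.5%.

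**Results with no drug effect.**

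| q | ρ | Per round: trial v comparison | False significance | Three rounds: trial v comparison | False significance |
|---|---|---|---|---|---|
| 2% | 0 | 4.0% v 2% | 28% | 11.4% v 5.9% | 65% |
| 2% | 0.5 | 3.0% v 2% | 12% | 8.7% v 5.9% | 25% |
| 5% | 0 | 9.75% v 5% | 59% | 26.5% v 14.3% | 95% |
| 5% | 0.5 | 7.4% v 5% | 22% | 20.5% v 14.3% | 51% |
| 10% | 0 | 19.0% v 10% | 87% | 46.9% v 27.1% | >99% |
| 10% | 0.5 | 14.5% v 10% | 37.5% | 37.5% v 27.1% | 76% |
| 10% | 0.8 | 11.8% v 10% | 11% | 31.4% v 27.1% | 20% |
| 10% | 1 | 10% v 10% | 5% | 27.1% v 27.1% | 5% |

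Comparing one interview with one interview gives an expected ratio of 1.0 and a 5% error rate at every q and ρ.

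**Break-even for the net direction.** With q = 10% and ρ = 0.5 in trial children, a comparison-group rate of 14.5% per interview would cancel the excess exactly.

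**The case against.** A reader might infer that the comparison is bound to show a drug effect. The documents do not support that. The excess arises only if two-visit cumulative incidence is set against one interview, and the protocol writes no analysis for this comparison. Section 3.9.1 describes the questionnaire's purpose in terms of prevalence, which suits a per-visit comparison. How visits are combined is commonly left to the SAP, which is not at hand. A single interview recalling everything the two trial visits cover would also remove the excess. This stands, and the point is therefore conditional. But an SAP can only choose among visits that took place: if comparison interviews fall on arbitrary days, there is no matched visit to select.

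A reader might also infer that the net bias must run against the drugs. That is not established. Comparison children receive no trial IPT during the season, and section 1.2.3 cites reductions in clinical malaria of 40% and 86%; malaria can cause fever and other listed symptoms. Nor is inclusion criterion 4, on health at entry, applied to them. Both may raise their symptom rate. In the other direction, trial children are observed after dosing (3.7) and identified by project staff at health centres (3.10). The balance cannot be worked out from the protocol.

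A third inference would be that the primary comparison is compromised, or that nothing else in the protocol addresses causality. Neither holds. All three randomised arms have the same visits, and the questionnaire staff are blinded to treatment group. Sections 3.5 and 3.16 presuppose case-level judgement of relatedness. The comparison group is supportive and appears in no objective, endpoint or sample-size calculation.

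Finally, the largest figures assume independent answers from the same child four days apart, which is generous. The correlated rows are the more cautious guide.

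**Conclusion.** The point holds in conditional form. Section 3.9.1 builds unequal ascertainment into the protocol's only untreated comparison for attributing minor symptoms to the drugs, and fixes neither a day nor a recall window that would allow like to be compared with like.

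If cumulative any-event incidence is used, the spurious-significance chance per round for backgrounds of 5% to 10% is about 22% to 38% at visit correlation 0.5 and 59% to 87% with independent visits. It approaches 5% as the correlation nears 1, and equals 5% under a matched-visit comparison or coinciding recall windows. These are ranges under assumptions, not estimates of what the trial will show. They isolate the effect of interview count and say nothing about the net direction once the other group differences are included.

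The comparisons of each alternative regimen with SP/AQ, the 286 per arm and the total of 1009 stand.

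**What to change.** In section 3.9.1:
- Schedule the comparison interview on the same post-round day as one trial visit, for example day 3, with the same recall window in both groups.
- State that the drug-relatedness comparison uses only that visit's answers from trial children, and that two-visit cumulative incidence is never set against one-visit incidence.

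This should be settled before fieldwork, since the interview day cannot be restored afterwards. It needs only wording and scheduling. The downside is that the other trial visit's data do not enter this one comparison; they remain available for the randomised comparisons.

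Interviewing comparison children on both days would also equalise ascertainment, at up to 286 × 3 = 858 further interviews, but is optional. Neither change removes the non-randomised differences between the groups, so the result should still be reported as supportive.

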Written informed consent will be obtained from the parent(s) or guardian(s) before a child is enrolled in the study. Approximately 1400 children aged between 1 to 5 years will be screened, of whom 1009 volunteers who meet the enrolment criteria will be enrolled in the study to receive SP plus AQ, SP plus PQP or Artekin TM. Clinic forms will be prepared and filled in by the study physician at screening. Each form will contain the subject’s initials, information about the subject’s date of birth, compound number, date of screening visit, whether the subject was enrolled or not and, when applicable, reasons for exclusion from the study based on medical history or physical or laboratory screening examination. A screening list will be prepared by the investigators as part of the routine source documentation. After review of the medical history, physical examination and laboratory results, reasons for non-eligibility will be documented on the list. Any clinically relevant finding will be treated at the discretion of the investigator. On entry into the trial a detailed clinical history, drug history, family history, and information on bednet usage and net impregnation will be obtained. The study physician will examine the child, document nutritional status and record the findings in a case report form. A finger-prick baseline blood sample will be obtained for determination of haemoglobin concentration and thick blood film preparation**.** Other investigations such as chest x-ray and urine examinations will be carried out as clinically indicated.

*3.3 Inclusion criteria*

1. Age between 1 to 5 years at enrolment.
2. Informed consent obtained from parents or legal guardians.
3. No current participation in another malaria intervention trial.
4. Free of obvious health problems as established by medical history and clinical examination before entering into the study.
5. Available for the duration of the study.

#

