***Withdrawal Criteria***

Study subjects may be withdrawn from the study for any one of the following reasons.

1. Withdrawal of parental / legal guardian’s consent.
2. Serious adverse event attributable to the study drug.
3. Loss to follow-up.

Children who develop adverse events attributable to study drugs should not receive further doses but should be followed-up to monitor safety up until the resolution of the adverse reaction.

*3.6 Randomisation*

Open-label, individual randomisation is proposed and will be done approximately three weeks before the first dose of IPTc administration planned for early September 2007. Study subjects will be individually randomised into either the AQ plus SP, PQP plus SP or ArtekinTM treatment groups in a 1:1:1 fashion. An independent statistician will generate the randomizing subject study number (SSN) that associates each SSN either to AQ plus SP, PQP plus SP or Artekin TM treatment groups and study subjects will be given treatment according to their randomisation group. A photo ID card will be given to all participants to facilitate identification at every contact, at home or in the health centres.

*3.7 Drug distribution at the health centres*

Study subjects and their parents will be informed about the date of treatment approximately one week before any intervention. Treatment will be given during the months of September, October and November. Drugs will be given at the nearest health centre by a designated member of staff. Tablets will be crushed, mixed with honey or suspended in water and given on a spoon. Staff who administer drugs at the health centre will play no further part in the trial. All participants will be kept under observation for 30 minutes after drugs are taken. In case of vomiting, the drug will be re-administrated. At the time of each monthly drug administration, a brief clinical assessment will be carried out. Children who are febrile will be screened for malaria using a rapid antigen test. Children found to have malaria will be treated with Lumefantrine-artemether (CoartemTM, Norvatis Pharma., Basel Switzerland).

*3.8 Treatment*

SP (tablets containing 500 mg sulfadoxine/ 25 mg pyrimethamine) will be given at an approximate dose of 1.25 mg pyrimethamine/25 mg sulfadoxine per kg stat.

Amodiaquine (200 mg base tablets) will be given at an approximate dose of 25 mg/kg over 3 days ( 10mg/kg D1, 10mg/kg D2 and 5mg/g D3).

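### The untreated group used to help judge drug-relatedness is not comparable with the trial children and is questioned half as often, so the drug-attributable excess has a bias of unknown size and direction

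*Protocol*

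**What the plan says.** Section 3.9.1 has trial children visited at home three and seven days after each round to complete a side-effects questionnaire. The field workers are blind to treatment group. The section then adds an outside group of 286 children, with the purpose "To help establish whether these adverse events are drug related". For this group, it says that "the same questionnaire will be administered once after each treatment round". It does not fix the day of that single interview. These children do not belong to the trial and are described as "recruited from nearby villages and matched for age to children in the trial".

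Entry rules differ. Section 3.3 requires a trial child to be "Free of obvious health problems as established by medical history and clinical examination before entering into the study", and section 3.4 adds organ-function and allergy exclusions. Nothing similar is stated for the outside children, and no IPT is stated for them.

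Section 3.9.1 defines an adverse event as "any unfavourable and unintended sign, symptom, syndrome, or illness that develops or worsens during the period of observation". Before dosing, section 3.2 plans a clinical history and a physician's examination at entry. Section 3.7 says: "At the time of each monthly drug administration, a brief clinical assessment will be carried out". The side-effects questionnaire itself is scheduled only after dosing.

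The primary endpoint (3.12.1) is the incidence of any adverse event. The powered comparisons (3.14) are each alternative regimen against SP/AQ.

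**The concern.** All three randomised arms are active. Randomisation can show which regimen causes more events, but not how many events any regimen causes over no drug. SP is in two arms and piperaquine in two, so harms they share partly cancel between arms. Section 1.2.3 notes that the 2006 tolerability data had no control group, and the 286 outside children fill that gap. The primary objective (2.1) is the safety and tolerability of the regimens, so this comparison matters.

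It differs from the trial arms in ways that move the background symptom rate:

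- **Health screening and malaria protection.** Fever, headache, weakness and vomiting are on the symptom list and can come from malaria or other illness. Healthier, protected trial children would have a lower background, which understates the drug excess.
- **Number of interviews.** Two per round against one gives trial children more chances to report, which overstates the excess.
- **Knowledge of treatment.** The trial is open-label (3.6), so caregivers know the child took a drug. The stated blinding covers treatment group only, so interviewers may well know that an outside child is untreated. Both would tend to raise reporting in treated children.

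Without the same questionnaire before dosing, a symptom already present on the dosing day is hard to tell from one that is new or worse.

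**Working it through.** **The plan's own figure.** For 20% against 10%, two-sided 0.05 and 90% power, the normal-approximation formula gives [1.960 × √(2 × 0.15 × 0.85) + 1.282 × √(0.20 × 0.80 + 0.10 × 0.90)]² / 0.10² = 266 per arm, or 286 with continuity correction. The total is 286 × 3 / 0.85 = 1009.4. Both stated figures reproduce. They concern the randomised arms and say nothing about the validity of the outside comparison.

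**Bias in the drug-attributable excess.** Section 3.9.1 gives one questionnaire per round to outside children and two to trial children. The protocol gives no background symptom rate, so the following are assumptions:

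- b: background risk of a reported symptom per questionnaire in outside children, 5% to 15%.
- rr: background in trial children relative to outside children, reflecting screening and IPT, 0.6 to 1.0.
- t: background captured in a trial child per round. If the second visit adds nothing, t = rr × b. If the two visits are independent, t = 1 − (1 − rr × b)².

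With drug effect D, the trial risk is 1 − (1 − t)(1 − D). The true excess subtracts t and the apparent excess subtracts b, so bias = t − b and D cancels. For example, with b = 10% and rr = 0.8, t is 8% or 1 − 0.92² = 15.4%, and the bias is −2.0 or +5.4 points.

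| b | rr | Bias in points, second visit adds nothing | Bias in points, visits independent |
|---|---|---|---|
| 5% | 0.6 | −2.0 | +0.9 |
| 5% | 0.8 | −1.0 | +2.8 |
| 5% | 1.0 | 0.0 | +4.8 |
| 10% | 0.6 | −4.0 | +1.6 |
| 10% | 0.8 | −2.0 | +5.4 |
| 10% | 1.0 | 0.0 | +9.0 |
| 15% | 0.6 | −6.0 | +2.2 |
| 15% | 0.8 | −3.0 | +7.6 |
| 15% | 1.0 | 0.0 | +12.8 |

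With independent visits the bias is zero at rr = (1 − √(1 − b)) / b, which is 0.506, 0.513 and 0.520 for b = 5%, 10% and 15%. It is downward only below those values.

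**One scenario with both signs.** Assume a 10% background in trial children, a 10% drug effect and 15% in outside children.

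- Second visit adds nothing: trial risk 1 − 0.9² = 19%. Apparent excess 19 − 15 = 4 points; true excess 19 − 10 = 9. Bias −5.
- Independent visits: trial risk 1 − 0.9³ = 27.1%. Apparent excess 27.1 − 15 = 12.1 points; true excess 27.1 − 19 = 8.1. Bias +4.

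**Scale.** For 19% against 15% with 286 children each, the 95% half-width is 1.96 × √(0.19 × 0.81/286 + 0.15 × 0.85/286) = 6.1 points. Biases in the table reach or exceed that sampling error, and a larger sample would not remove them.

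**The case against.** The strongest reply is that little depends on this group. The protocol says it helps to establish drug-relatedness, not that it decides it. The primary endpoint counts any adverse event and needs no attribution, and the powered comparisons are randomised. Causality is also judged child by child: section 3.5 refers to events attributable to study drugs, and the Local Safety Monitor receives grade 3 events thought to be related. All of this stands and limits the point to attribution against no drug.

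Three stronger readings are tempting, and the documents do not support them.

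- A reader might infer that the design makes all three regimens look safer than they are. That counts only the downward forces. Double questioning and open-label reporting act the other way, and the sign cannot be fixed from the protocol. Nor can the Summary's statement that "IPTc provided between 40% - 86% protection against clinical malaria" settle it. By section 1.2.3 the 40% came from SP alone in Mali and the 86% from SP with one dose of artesunate in Senegal. Neither is a trial regimen, and both figures concern clinical malaria rather than reported symptoms.
- A reader might infer that nothing is recorded before dosing. Sections 3.2 and 3.7 plan an entry history, an examination and a brief assessment each round. Only the matching questionnaire is absent.
- A reader might take it as stated that the outside children are unscreened and unprotected. That is a fair inference from silence, but the protocol does not say so.

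A further objection concerns the remedy: change from before to after dosing is not a clean estimate of background. Doses are curative (1.2.1), so clearing an existing infection could mask a drug effect, and piperaquine, with a half-life of about 17 days (1.2.4), is still present at later rounds. This stands. The pre-dose questionnaire should identify symptoms already present, and should be asked in both groups.

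**Conclusion.** The concern holds in a limited form. The outside group is matched on age only, has no stated health screen or IPT, and is questioned once per round against twice. The questionnaire has no pre-dose counterpart. The estimated drug-attributable excess is therefore biased by an unknown amount in an unknown direction.

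Under the assumed values (b from 5% to 15%, rr from 0.6 to 1.0, the second visit anywhere from redundant to independent) the bias lies between −6.0 and +12.8 percentage points. Reporting differences from knowledge of treatment are not in that range and would tend to move it upward. The protocol supplies none of these inputs, so the range illustrates the problem and does not estimate it.

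The randomised comparison of any adverse event, and its sample size, are not affected. This is a worthwhile, inexpensive improvement to the attribution part of the safety objective. It should be made before the first round, because a questionnaire not given before dosing cannot be recovered in analysis.

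**What to change.** Amend section 3.9.1 as follows.

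1. Apply the health criteria of sections 3.3 and 3.4 to the 286 comparison children.
2. Question them on the same days and with the same recall period as trial children. Alternatively, keep one interview, fix its day, and compare it only with the matching visit in trial children.
3. Give the same questionnaire before dosing at each monthly visit to trial children, and at the corresponding time to comparison children, so that symptoms already present are not counted as new events.
4. Report the external comparison as supportive, and state that the difference in malaria protection remains.

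Cost: a few minutes per trial child at three visits already scheduled, at most 1009 × 3 = 3,027 short questionnaires; a brief history and examination for 286 children; and, for those children, 286 × 3 = 858 short interviews before the rounds plus another 858 if a second post-round interview is added. The single-matched-visit option avoids the second 858. No blood samples and no new trial visits are needed.
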